### Stage II: Follow-up interventions in the first 12 weeks after discharge to home

Intervention nurses will provide participant dyads with phone support and face-to-face meetings in outpatient clinics over a 12-week period as follows:
Weekly telephone support: Participant dyads will receive a weekly telephone call at home from an intervention nurse. Participants will be encouraged to discuss concerns and problems arising from transition care. They will also be provided with resources and strategies to resolve problems. An intervention nurse will motivate participants to monitor their care activities and outcomes towards their transition care goals. Each phone call will last about 10–15 min. Participants can also seek additional phone help from an intervention nurse when necessary.Bi-weekly face-to-face coaching activities at an outpatient department: Stroke survivors will engage in rehabilitation or have an appointment with specialists at the outpatient clinic bi-weekly. An intervention nurse will use this opportunity to meet with participant dyads. Participant dyads will be asked to bring their coaching diary to this meeting to lead discussion about any concerns and problems they have encountered. An intervention nurse will coach participants to develop problem-solving skills based on their needs, introduce resources to them, reinforce self-care knowledge and skills, and motivate them to self-monitor progress and outcomes towards care goals.

### Usual care

Participants in the usual care group will receive the usual transitional discharge plan that includes verbal stroke-related education and a follow-up telephone call at the end of the first and the fourth week after discharge to home. For usual care, other registered nurses, who are not intervention nurses, will conduct the discharge plan and follow-up.

### Outcomes measures

Outcome measures are based on hypotheses of this RCT. The effects of the intervention will be measured at baseline, 12 weeks and 24 weeks. The general procedure of data collection and assessments is presented in Fig. 2 (the SPIRIT figure).

**Fig. 2 Fig2:**
[figure not shown]
SPIRIT figure: general procedure of enrolment, intervention and assessment

### Outcomes of stroke survivors

#### Primary outcomes

1.1.Self-efficacy: This outcome will be measured using the Stroke Self-efficacy Questionnaire (SSEQ). The SSEQ consists of 13 items to test self-efficacy in two dimensions: activity domain (7 items) and self-management (5 items) [27]. It has been translated into Chinese and proven to be reliable and valid for the Chinese population with the Cronbach’s α 0.972, and a test-retest reliability coefficient of 0.806 [28].

#### Secondary outcomes

2.1Quality of life: This outcome will be measured using the short version of the Stroke-Specific Quality of Life Scale (SSQoL-12). The SSQoL-12 is a self-assessment scale comprising physical domain (6 items) and psychosocial domain (6 items) [29]. The SSQoL-12 has good criterion validity and internal consistency (Cronbach’s α 0.77–0.89).2.2Functional ability: This outcome will be measured using (1) the Chinese version of the Barthel Index (BI) for ADL, (2) the Multilevel Lawton Instrumental Activities of Daily Living (Lawton IADL), and (3) the Social Support Rating Scale (SSRS). The BI comprises 10 items and is a valid tool to evaluate the ADL of stroke survivors [30, 31]. It has been translated into Chinese with acceptable internal consistency (Cronbach’s α of 0.916) [32]. The Lawton IADL is an appropriate instrument with eight categories to assess independent living skills [33]. It has been used and proven in the Chinese population with a satisfactory Cronbach’s alpha of 0.739 [34]. The SSRS was developed in China and is widely used with high validity (Cronbach’s alpha 0.83 to 0.90) and reliability (test–retest reliability 0.92) [35, 36].2.3Stroke-related health knowledge: This outcome will be measured using the Chinese Stroke Prevention Knowledge Questionnaire (SPKQ). The SPKQ comprises 25 items using close-ended questions to assess patients’ stroke-related knowledge. It has been used in the Chinese population with a validity index of 0.89 and Cronbach’s α of 0.86 [37].2.4The number of deaths, adverse events and unplanned hospital admissions: The adverse events will be limited to secondary strokes, falls, ulcers and urinary tract infections to reflect the nurse-led intervention to prevent post-stroke associated complications. These outcomes will be recorded by participants on the “Adverse Events Form” and verified by an intervention nurse.

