#### Inclusion criteria for health coaches

Health coaches will be trained intervention nurses from each participating ward of the two hospitals, and they will conduct all interventions in this study. The eligibility criteria for health coaches are (1) a registered nurse; (2) at least a bachelor’s degree in nursing; and (3) at least 5-years work experience in the care of stroke survivors.

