### Evaluator blinding

Participant dyads and intervention nurses will not be blinded due to the nature of the intervention. However, the researcher, who will collect the outcome assessments and undertake data entry and analysis, will remain blinded to treatment allocations. Intervention nurses, who will conduct the telephone and outpatient clinic follow-ups, will not be blinded as they will need to update participant information and maintain the intervention and service.

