Fidelity of implementation is an important factor in the intervention’s effectiveness [55]. There is little consensus about key factors affecting intervention fidelity. However, the domains of fidelity, such as study design, training and intervention delivery, have been considered and will be addressed through the following strategies [56]. First, the researchers in this study have adapted the health coaching definition, self-efficacy theory and CALO-RE taxonomy that standardizes health coaching intervention design and behavior change techniques [45, 46]. Second, the training of intervention nurses to standardize health coaching interventions will improve adherence to the intervention protocol. Third, intervention nurses will encourage stroke survivors to record self-care in their health coaching diary to self-monitor processes to achieve set goals. In addition, open-ended questions will be provided at the end of the trial to analyze factors that may affect intervention fidelity.

The protocol has some limitations. First, although all outcomes will be recorded by an independent researcher to minimize the risk of bias, participant dyads and health coaches cannot be blinded due to the nature of the intervention. Second, successful behavior modification is a sustainable long-term process. However, the duration of the intervention and follow-up in this study are 12 and 24 weeks respectively. Therefore, the long-term effectiveness of health coaching in stroke rehabilitation needs to be further explored. In addition, future studies need to consider the measures of cardiovascular events as part of study outcomes when it is appropriate.

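### Deaths, adverse events and admissions are verified by the unblinded coach, whose scheduled contact after allocation is with the coached arm only; this conflicts with the claim of independent recording

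*Protocol article*

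**What the plan says.** Item 2.4 of the secondary outcomes covers deaths, adverse events and unplanned admissions, and gives the only account of how they are captured: "These outcomes will be recorded by participants on the “Adverse Events Form” and verified by an intervention nurse". It restricts the event list by reference to what the coaching aims to prevent: "The adverse events will be limited to secondary strokes, falls, ulcers and urinary tract infections to reflect the nurse-led intervention".

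On who verifies:
- Inclusion criteria for health coaches: "Health coaches will be trained intervention nurses from each participating ward of the two hospitals".
- Evaluator blinding: "Intervention nurses, who will conduct the telephone and outpatient clinic follow-ups, will not be blinded". The same section says that the researcher who collects outcome assessments stays blinded.

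On contact after discharge:
- Stage II gives the coached arm "phone support and face-to-face meetings in outpatient clinics over a 12-week period". Specifically, "Participant dyads will receive a weekly telephone call at home from an intervention nurse", and the clinic meetings are bi-weekly.
- Usual care provides two telephone calls, at the end of weeks 1 and 4, and "other registered nurses, who are not intervention nurses, will conduct the discharge plan and follow-up".

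The limitations paragraph of the Discussion offers as a safeguard that "all outcomes will be recorded by an independent researcher to minimize the risk of bias".

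**The concern.** Two features combine. First, the person who confirms whether a complication occurred is the unblinded nurse whose coaching is meant to prevent it. Second, the schedule brings that nurse into regular contact with one arm only. Coached dyads are also shown in hospital how to recognise the complications that are later counted (Table 1, complication prevention), so their self-recording may differ too.

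These mechanisms pull in different directions. More contact and better recognition tend to raise the recorded count in the coached arm. Lenient confirmation by the coach tends to lower it. An observed difference between arms, or the absence of one, could therefore partly reflect how events were found and confirmed. Because neither the direction nor the size is known, the analysis cannot correct for it. A reader who relies on the Discussion would believe that independent recording had removed the problem.

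**Working it through.** **Step 1. Who verifies.** Item 2.4 names an intervention nurse. The health-coach criteria identify intervention nurses with the coaches, and the blinding section says they are unblinded. So verifier = coach = unblinded. This needs no inference.

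**Step 2. Scheduled contacts with the verifier after allocation, per dyad.**
- Coached arm, after discharge: 12 weeks × 1 call = 12; 12 ÷ 2 = 6 clinic meetings; 12 + 6 = 18.
- If bi-weekly meant twice a week: 12 + 24 = 36.
- With the two in-hospital coaching sessions added: 18 + 2 = 20.
- Usual care: 0 with an intervention nurse; 2 calls from other nurses.

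The imbalance is confined to the coaching period. No contact with the verifier is scheduled in either arm between weeks 12 and 24. Before allocation there is contact in both arms, because intervention nurses screen, consent and allocate every dyad (Recruitment).

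**Step 3. Overlap of prevention targets and counted events.** Table 1 teaches coached dyads to prevent, recognise and manage four complications: recurrent stroke, pressure sores, falls and urinary infection. Item 2.4 counts the same four.

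**Step 4. The passages side by side.** Item 2.4: participants record and the coach verifies. Evaluator blinding: a blinded researcher collects outcome assessments. Discussion: an independent researcher records all outcomes. For these events the first and third cannot both be literally true, and the second is hard to square with the first.

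**Step 5. Size.** The plan gives no event rate, detection rate or other figure to reproduce on this point. The following is an illustration on assumed inputs: 70 per arm (the planned number), a true risk of 20% in both arms, and 95% of events captured in the coached arm. Recorded risk = 0.20 × capture, and the false risk ratio is the ratio of the capture rates.

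| Usual-care capture (assumed) | Expected events, coached vs usual care | False risk ratio | Chance of a false significant excess in the coached arm |
|---|---|---|---|
| 80% | 13.3 vs 11.2 | 0.95/0.80 = 1.19 | 6.8% |
| 70% | 13.3 vs 9.8 | 0.95/0.70 = 1.36 | 12.2% |
| 50% | 13.3 vs 7.0 | 0.95/0.50 = 1.90 | 32.6% |

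With equal capture the last column would be 2.5%. It is the normal-approximation power for two proportions at two-sided 0.05: Φ{(p1 − p2 − 1.96·√[2p̄(1 − p̄)/n]) / √[(p1(1 − p1) + p2(1 − p2))/n]}. For the 70% row: p1 = 0.19, p2 = 0.14, p̄ = 0.165, n = 70, giving (0.050 − 0.123)/0.0626 = −1.17 and Φ = 0.122.

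If lenient confirmation dominated and the capture rates were swapped, the ratios would invert to 0.84, 0.74 and 0.53, an apparent benefit. The documents do not say which pattern, if either, would occur.

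**The case against.** The strongest reply is that item 2.4 sets one procedure for the whole trial. Both arms have the same form, the participant records first, and the same type of nurse only confirms. The article does not say when the nurse verifies or from what source. Contact with usual-care dyads for that purpose is not described, but it is not excluded. The usual-care section hands only the discharge plan and routine follow-up to other nurses, and the full protocol may hold more detail. On this view unequal ascertainment is an inference. That is correct, and the point is worded accordingly. What survives is that the named verifier is unblinded and that the only contact scheduled for that nurse after allocation is with one arm.

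A second reply is that an independent researcher recording outcomes could mean collecting and entering forms that participants have already completed. That softens the conflict, but the Discussion presents the arrangement as protection against bias, and verification by the coach undercuts that protection.

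A reader might go further in four ways that the documents do not support:
- That deaths cannot be recorded because the patient is the one recording. Caregivers are participants within the dyad and can record a death.
- That the verifying nurse never meets usual-care dyads. This is true only of scheduled contact after allocation.
- That a particular false risk ratio is to be expected. Every ratio above rests on assumed capture rates.
- That the event comparison is beyond interpretation. Deaths and admissions are harder facts, easier to check and less exposed than falls, ulcers or urinary infections.

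**Conclusion.** The point holds in limited form. Stated outright: these outcomes are verified by the unblinded coach, and the Discussion's account of independent recording does not match. Inferred: with about 18 scheduled post-discharge contacts in one arm and none after allocation in the other (bi-weekly taken as fortnightly), ascertainment over the first 12 weeks is probably unequal. Direction and size are unknown.

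The exposure is to one group of secondary outcomes. The primary outcome, stroke self-efficacy, is self-completed and returned by post to the researcher, and the sample size rests on it alone; neither is affected. This should be fixed, but it does not threaten the trial's main conclusion.

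**What to change.** 1. Include the Adverse Events Form in the questionnaires already mailed to participants at 12 and 24 weeks (Data collection methods), identically in both arms, for return to the blinded researcher.
2. Have that researcher, not the intervention nurse, verify events by the same method in both arms, with a check of de-identified records of the two hospitals where feasible.
3. Base the between-arm comparison on this common source. Log events first learned at coaching contacts separately.
4. Reconcile item 2.4, the blinding section and the limitations paragraph so that they describe one procedure.

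The cost is one form in an existing mailing and a record check. Recall by post will lose some minor events, and the two hospitals' records will miss events treated elsewhere, but the procedure is the same in both arms. Two things remain: reporting is still by unblinded participants, and coached dyads are still taught to recognise these events; both belong in the limitations.

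On timing, recruitment was expected to finish on 10 October 2019. On that schedule the last 12-week point falls about 2 January 2020 (84 days later), before the date of Version 2.0 (20 January 2020). Where a mailing has already gone out, the blinded record check can still be done retrospectively.

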### Outcomes of Caregivers

Self-efficacy: This outcome will be measured using the Generalized Self-Efficacy Scale (GSES). It contains 10 items to measure people at risk for coping deficiencies. With its highly validity, the GSES has been widely used around the world. It has been used in the Chinese population with a Cronbach’s α of 0.89. Higher scores indicate better self-efficacy [38, 39].Caregiver-related burden: This outcome will be measured using the Chinese version of the Modified Caregiver Strain Index (CSI). The CSI contains 13 items including financial, physical, psychological, social and personal domains. It is rated on a scale from 0 (No) to 2 (Yes). The total score ranges from 0 to 26 points, with higher scores indicating greater caregiver burden [40]. It was validated in the Chinese population with a Cronbach’s alpha of 0.91 [41].

### Sample size

The sample size is estimated on the basis of the primary outcome, stroke survivors’ self-efficacy, measured by the SSEQ [27]. We generated the estimated effect size of 0.5 based on a 7.5 point between-group change in SSEQ from baseline reported in a similar RCT by Lo et al. [42]. We also estimated a pooled SD of 6.42 based on the 95% confidence interval of the SSEQ score reported in the study. A type I error of alpha 0.05 and a power of 80% were used in the sample size calculation. We expect a 10% dropout rate. Therefore, we will require 70 dyads per treatment group. In total, we will recruit at least 140 participant dyads into the study.

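### The sample-size inputs contradict each other: 7.5 SSEQ points over an SD of 6.42 is an effect size of 1.17, not the 0.5 on which 70 per group rests

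*Protocol article*

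**What the plan says.** The whole calculation stands in one paragraph, the Sample size section of the protocol article. It is based on the primary outcome, stroke survivors' self-efficacy on the SSEQ. The effect size and the difference are given together: "We generated the estimated effect size of 0.5 based on a 7.5 point between-group change in SSEQ from baseline". Both are attributed to a similar published trial. The next sentence supplies the SD: "We also estimated a pooled SD of 6.42 based on the 95% confidence interval of the SSEQ score reported in the study". The error rates follow: "A type I error of alpha 0.05 and a power of 80% were used in the sample size calculation". The result is: "We expect a 10% dropout rate. Therefore, we will require 70 dyads per treatment group". The total is at least 140 dyads.

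The paragraph does not describe 0.5 as a cautious or conventional value. It presents 0.5 as derived from the 7.5-point difference. No other section gives a different SD or target difference for the SSEQ.

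**The concern.** A standardised effect for two means is the difference divided by the SD, so any two of the three figures fix the third. Here all three are stated and they disagree by more than a factor of two. At least one must be wrong, or 0.5 was not obtained in the way the text says.

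This is the only justification given for the sample size. The Data analysis section will report estimated mean differences with 95% confidence intervals, and readers will want to set these against the difference the trial was designed to detect. From this paragraph they cannot tell whether 80% power was meant for 7.5 SSEQ points or for about 3.2.

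**Working it through.** **Inputs, all from the Sample size section:** difference 7.5 points, SD 6.42, effect size d = 0.5, alpha 0.05, power 80%, dropout 10%, 70 per group. The Randomization section gives 1:1 allocation. The article does not say whether alpha is one- or two-sided. I take it as two-sided, because that reproduces the stated number. One-sided gives 50 evaluable and 56 recruited per group, which does not.

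**1. Reproduce the plan's figure.** With n per group = 2(z₀.₉₇₅ + z₀.₈₀)²/d² and d = 0.5:

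- 2 × (1.960 + 0.842)²/0.25 = 62.8, rounded up to 63.
- With 10% dropout: 63/0.9 = 70, an exact match.
- The t-based calculation gives 63.8, so 64, and 64/0.9 = 71.1, so 72.

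The 70 is therefore correct for d = 0.5, and the dropout step is correct too.

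**2. Compute the effect size from the stated difference and SD.** 7.5/6.42 = 1.168.

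**3. Sample size from the stated difference and SD.**

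- Normal approximation: 2 × (1.960 + 0.842)²/1.168² = 11.5, so 12 evaluable, and 12/0.9 = 13.3, so 14 recruited per group.
- t-based: 12.5, so 13 evaluable, and 13/0.9 = 14.4, so 15 recruited per group.

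**4. What would make d = 0.5 true.**

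- Keep 7.5 points: SD = 7.5/0.5 = 15.
- Keep SD 6.42: difference = 0.5 × 6.42 = 3.21 points.
- Ratio of the two differences: 7.5/3.21 = 2.3.

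**5. Power with 63 evaluable per group.**

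| Difference | SD | d | Power, normal | Power, t |
|---|---|---|---|---|
| 7.5 | 15 | 0.5 | 80.1% | 79.5% |
| 3.21 | 6.42 | 0.5 | 80.1% | 79.5% |
| 7.5 | 6.42 | 1.168 | >99.99% | >99.99% |

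The article states the inputs of the last row but claims the power of the first two.

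**6. Could score versus change explain the gap?** The 7.5 is a difference in change from baseline, while the 6.42 is described as coming from the interval of the score. Suppose 6.42 is the SD of a single score, equal at baseline and follow-up with correlation r. The SD of the change is then 6.42 × √(2(1 − r)):

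| r | SD of change | d for 7.5 points |
|---|---|---|
| 0 | 9.08 | 0.83 |
| 0.3 | 7.60 | 0.99 |
| 0.5 | 6.42 | 1.17 |
| 0.7 | 4.97 | 1.51 |

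Even at r = −1 the SD of the change is only 12.84, so d = 7.5/12.84 = 0.58. Reaching 15 would need r = 1 − 225/(2 × 6.42²) = −1.73, which is impossible. Under this assumption, the score-versus-change distinction does not give 0.5.

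**The case against.** The best defence is that the number that matters is right. An effect size of 0.5 is stated, 70 per group follows from it exactly, and 80% power belongs to it. The fault lies only in where the 0.5 comes from. For 7.5 points, the trial has about 80% power if the SD is 15 and nearly 100% if it is 6.42, so on neither reading is it too small. If the SD alone was misderived, the 7.5, the 0.5 and the 140 all stand. The results will carry confidence intervals, which can be compared with 7.5 points whatever SD was assumed in planning. Recruitment was also expected to finish in October 2019, before the protocol version dated January 2020, so the number recruited is not in play.

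All of this stands and limits the consequence: the point does not call for a different sample size, and a null result would remain interpretable from its interval. The defence does not remove the contradiction. The text says 0.5 was generated from the 7.5-point change and does not call it a cautious choice. Condensing a longer protocol could explain an omission, but here incompatible figures are printed side by side.

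One further caution is fair. The article does not say whether the confidence interval belonged to a baseline, follow-up or change score, so that mismatch is only a possibility.

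**Conclusion.** The concern holds. The difference of 7.5, the SD of 6.42 and the effect size of 0.5 are mutually inconsistent: the first two give 1.17. The 70 per group rests on 0.5 alone, while the stated difference and SD would need 12 to 13 evaluable per group, or 14 to 15 with dropout. On the SSEQ point scale, 80% power refers to 7.5 points if the SD is 15 or to 3.2 points if it is 6.42, and neither pair is stated.

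This rests on a two-sided test and a comparison of two means. The article alone cannot show which figure is wrong. An error in turning the confidence interval into an SD is plausible, but it is an assumption that needs the cited trial to check. The justification is wrong as written and must be corrected. The sample size itself need not change.

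**What to change.** Return to the cited trial and recheck how its 95% confidence interval was converted into an SD. Confirm whether the interval belongs to a group mean, a mean change or a difference between groups, and which sample size was used in the conversion. Use the SD of the quantity to be analysed. Then restate the paragraph with one coherent set of difference, SD and effect size, and delete the figure that does not survive.

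Depending on the recheck, the text could read along one of these lines:

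- If 6.42 is right: 70 dyads per group (63 evaluable) give 80% power, at two-sided alpha 0.05, for 3.2 SSEQ points with SD 6.42 (effect size 0.5); power for 7.5 points exceeds 99%.
- If 7.5 and 0.5 are right: 70 dyads per group (63 evaluable) give 80% power, at two-sided alpha 0.05, for 7.5 SSEQ points with SD 15.

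These are illustrations that keep 70 per group. Neither SD 15 nor 3.2 points should be adopted merely because it makes the arithmetic close. If the recheck gives another SD, state that SD and the power it implies. If 0.5 was chosen deliberately as smaller than the published effect, say so and give the reason.

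The cost is a check of one source and the rewriting of two sentences, with no change to recruitment.
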